### 2.9. Adverse events

A safety questionnaire will be administered to all participants prior to the administration of the first PA or EMT to reduce the risk of possible symptoms, including dry eyes, headache, and irritability, and will be recorded at the end of each session. Descriptive statistics will be provided for all adverse events.

The following measures will be taken to prevent these events: (a) prior to the intervention, the investigator will communicate adequately to ensure that the patient is in a good state after rest; (b) during the intervention, the investigator will closely monitor the patient's condition and keep records; (c) if the patient feels any discomfort, the intervention will be suspended immediately, the intervention protocol will be adjusted (by increasing the interval of rest), or the intervention will be stopped. If a serious adverse event occurs, we will seek professional evaluation, cover the cost of treatment for the adverse event caused by the trial, and provide some financial compensation.

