### 2.10. Dropout criteria

The intervention will be discontinued if the subject meets one or more of the following criteria: (a) the subject has poor compliance and fails to perform the treatment as required, e.g., the subject does not cooperate with the investigator or the subject does not come to treatment on time; (b) medical records are incomplete and affect efficacy or safety evaluation; (c) subject voluntarily withdraws; (d) subject experiences an adverse event (including episodes of ocular pain, headache, and irritability); and (e) the subject has a severely progressive disease or some comorbidity, complications, or specific physiological changes.

Patients who drop out will not be included in the efficacy analysis; if they drop out for reasons such as the occurrence of an adverse event, they will be included in the safety analysis.

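### Whether a dropout enters the safety analysis depends on the reason for leaving, not on having been treated, so adverse-event proportions can be distorted in either direction

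*Protocol article*

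**What the plan says.** Section 2.10 lists five grounds for discontinuation. Three are not adverse events by name: (a) "the subject has poor compliance and fails to perform the treatment as required"; (b) "medical records are incomplete and affect efficacy or safety evaluation"; and (c) "subject voluntarily withdraws". Ground (d) is an adverse event: "subject experiences an adverse event (including episodes of ocular pain, headache, and irritability". Ground (e) is progressive disease, comorbidity or complications.

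Two analysis rules follow. For efficacy: "Patients who drop out will not be included in the efficacy analysis". For safety: "if they drop out for reasons such as the occurrence of an adverse event, they will be included in the safety analysis".

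Section 2.9 has symptoms recorded after every session and promises a summary without any restriction by patient: "Descriptive statistics will be provided for all adverse events". Section 2.11 adds that as much data as possible will be collected from participants who discontinue or deviate. The abstract limits the final analysis to patients who completed all treatment and assessment sessions. No section says that the safety analysis covers everyone who was treated.

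**The concern.** The safety sentence is conditional. A condition on the reason for leaving has a purpose only if some dropouts do not meet it, and grounds (a) to (c) are the obvious candidates. Yet these patients may have had several sessions, with symptoms recorded after each. A patient with a headache in an early session who later withdraws is covered by Section 2.9 but may not be covered by Section 2.10.

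The label given to a departure can also be a matter of judgement. Irritability is a listed adverse event, while failure to cooperate with the investigator counts as poor compliance, so one patient could fit either. Under Section 2.5 only the outcome assessor is blinded. Nothing in the article ensures that reasons are assigned without knowledge of the arm.

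What is at stake is the comparison of adverse-event proportions between arms. The Discussion says that patient tolerance has to be considered when therapies are combined, and names active participation in both therapies as a possible limitation. Its reassurance comes from the few patients who had completed the intervention. A reason-dependent safety set leans towards the same completer view.

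**Working it through.** **Inputs**

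- Section 2.4: 20 per group before dropout, 10% dropout, 22 per group, 88 in total.
- Sections 2.9 and 2.10: the recording and inclusion rules above.
- Not given in the article: any adverse-event rate or safety denominator. The event counts below are assumptions.
- Also assumed: all 22 randomised patients in an arm start treatment.

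**The plan's own figures.** 20 × 1.10 = 22 per group, and 22 × 4 = 88. (Section 2.1 gives a total of 72. I use 88, as do the abstract and Sections 2.4 and 2.5.) These figures reproduce. No stated safety figure exists to check.

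**Patients the rule could remove.** 22 × 0.10 = 2.2, so about 2 dropouts per arm; 88 × 0.10 = 8.8, so 8 to 9 in total. Depending on the reasons, the safety denominator lies between 22 − 2 = 20 and 22 per arm, or about 88 − 9 = 79 to 88 overall.

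**Effect on one arm.** Let *k* be the dropouts excluded, *E* the patients with an event among those retained, and *v* those with an event among the excluded.

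- Reported proportion = *E* / (22 − *k*)
- Proportion in all treated = (*E* + *v*) / 22

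With an assumed *E* = 4:

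| Excluded (*k*) | Excluded with an event (*v*) | Reported | All treated | Reported minus all treated |
|---|---|---|---|---|
| 0 | 0 | 4/22 = 18.2% | 4/22 = 18.2% | 0.0 points |
| 1 | 0 | 4/21 = 19.0% | 4/22 = 18.2% | +0.9 |
| 1 | 1 | 4/21 = 19.0% | 5/22 = 22.7% | −3.7 |
| 2 | 0 | 4/20 = 20.0% | 4/22 = 18.2% | +1.8 |
| 2 | 1 | 4/20 = 20.0% | 5/22 = 22.7% | −2.7 |
| 2 | 2 | 4/20 = 20.0% | 6/22 = 27.3% | −7.3 |

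(Differences are taken before rounding.)

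**Sensitivity to the assumed *E*, with *k* = 2.** If *E* = 2, the report shows 2/20 = 10.0% against 2/22 = 9.1% to 4/22 = 18.2%. If *E* = 6, it shows 6/20 = 30.0% against 6/22 = 27.3% to 8/22 = 36.4%. The pattern is the same: losing event-free patients inflates the proportion modestly, and losing patients with events deflates it by more.

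**The case against.** A reader might infer that the plan admits only adverse-event dropouts, that other patients' events are certain to be lost, and that the resulting rates must be wrong. The article does not support that. Four points count against it.

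1. The sentence does not say *only*. Its list of reasons is open, and other dropouts are not expressly excluded. This stands. However, an open list leaves inclusion to a later judgement about reasons, which is itself a weakness.
2. Section 2.9 promises statistics for all adverse events, and Section 2.11 promises continued data collection. This stands as far as the events are concerned: they should be on record and may well be described. But Section 2.11 does not say who enters the safety analysis, and neither section gives a denominator.
3. Ground (d) makes an adverse event itself a reason to discontinue, and a patient may meet more than one ground. Many patients with symptoms would therefore fall in the group that is expressly included. This makes the lower rows of the table less likely, but does not rule them out. Section 2.9 also allows the intervention to be suspended or adjusted after discomfort, so a patient could have an event, continue, and leave later under another label. Sections 2.9 and 2.10 need to be reconciled on this; I take no view on which should govern.
4. Exact analysis-set definitions are often left to a fuller document, and the trial's stated aim is efficacy, with safety only described. Both are fair. The point here is not a missing definition, though, but a rule that the article states and that makes inclusion depend on the wrong thing.

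**Conclusion.** The concern holds in a limited form. Section 2.10 ties safety inclusion to the reason for leaving, and this does not agree with the scope promised in Section 2.9. The denominator is the firmer problem. There is some remaining risk to the numerator, reduced by ground (d) and by recording after each session.

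At the planned dropout, with both of an arm's dropouts leaving for other reasons and 4 of the 20 retained having an event, the reported proportion is between 1.8 points too high and 7.3 points too low. The error is zero if all dropouts are of adverse-event type. These sizes rest on assumed event counts and on all 22 patients starting treatment. The article states no adverse-event rate, so no published figure is shown to be wrong. The efficacy conclusions are not affected by this point. The rule should still be changed, because reasons for leaving may differ between arms and the remedy is cheap.

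**What to change.** Replace the safety sentence in Section 2.10 with wording such as: *The safety set comprises all participants who start at least one session of their allocated treatment (control: conventional rehabilitation after randomisation), whatever their reason for stopping. Adverse events will be reported by arm as the number of patients with an event over the number treated.* Section 2.9 can then refer to this set.

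The cost is one sentence. In the three active arms no new data are needed, since symptoms are already to be recorded at each session. One check is needed: Section 2.9 links the symptom questionnaire to the first PA or EMT, which control patients do not receive. Confirm that the control arm has the same recording before its proportions are compared with the others. If it does not, report it separately and say so.

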### 2.11. Data collection and management

The trial process will be recorded *via* the audio or written form to ensure the authenticity of the intervention. A case report form (CRF) will be used to collect data. Two data managers will enter the data from the CRF into a computer database and cross-check the electronic data for uniformity. All data will be confidential to those outside the study, except for the ethics committee. Experimental data will be used to write clinical research studies. During the course of the study, if subjects discontinue or deviate from the intervention protocol, we will collect as much data as possible for further analysis.

We will use the following methods to facilitate participants' completion of the trial and follow-up: (a) enhance communication between investigators and patients and obtain patients' cooperation whenever possible and (b) provide relevant test results to study patients free of charge.

### 2.12. Data analysis

IBM SPSS Statistics for Windows, Version 26.0 (IBM Corp., Armonk, NY, United States) will be used for statistical analysis. 2-tailed *P* < 0.05 will be considered a statistically significant difference. Continuous variables will be expressed as mean with standard deviation or median with interquartile range, whereas categorical data will be expressed as counts and percentages. Baseline comparisons will be used to examine potential differences between 4 groups. Age, time of onset, and MMSE will be analyzed by ANOVA or Kruskal-Wallis test. Sex, cause of damage will be measured using Chi-square tests. The Kolmogorov-Smirnov test will be used to evaluate the normality of distributions. If a normal distribution is confirmed, one-way ANOVA will be used to examine the effectiveness of intervention between the 4 groups at T1, T2, with Bonferroni correction for multiple comparisons as a *post hoc* test. Otherwise, Kruskal-Wallis (non-parametric test) will be used.

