### 2.4. Sample size estimation

In the preexperiment, the changes in BIT-C scores before and after the intervention were 39.33 ± 18.717 for the combined intervention group, 26.33 ± 7.638 for the eye-movement training group, and 20 ± 2.828 for the PA training group. Using the PASS software, the probability α of occurrence of the Type I error was set to 0.05, the probability β of occurrence of the Type II error was calculated as 0.2, the calculation results showed that the combined intervention and eye-movement training groups required 20 samples each, and 9 samples were required for each of the combined intervention and PA training groups. Therefore, taking into account a 10% sample dropout rate, the total sample size was finally determined to be 88 cases, with 22 cases in each group.

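### The analysis picks a pooled-variance ANOVA on a normality check alone, although the plan's own pilot SDs of BIT-C change make equal variances doubtful

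*Protocol article*

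**What the plan says.** Section 2.12 (Data analysis) makes the choice of efficacy test depend on a Kolmogorov-Smirnov test of normality: "If a normal distribution is confirmed, one-way ANOVA will be used" to compare the four groups at T1 and T2, with Bonferroni post hoc comparisons. Otherwise Kruskal-Wallis is used. The significance rule is "2-tailed *P* < 0.05 will be considered a statistically significant difference". Nothing in the rule depends on the variances, and the section does not say whether the analysed variable is the score at the visit or the change from baseline.

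Section 2.4 (Sample size estimation) gives pilot results for BIT-C change: "39.33 ± 18.717 for the combined intervention group", "26.33 ± 7.638 for the eye-movement training group" and "20 ± 2.828 for the PA training group". It gives no control-arm result and no number of pilot patients.

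**The concern.** One-way ANOVA with Bonferroni post hoc tests puts one mean square, averaged over all four arms, into the standard error of every pair. If the combined arm varies much more than the others, averaging in the low-variance arms can make the standard error too small for pairs that include the combined arm and too large for pairs that do not. Equal allocation gives the overall F test some protection. It does not protect pairwise tests that share the four-arm mean square.

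The combined-arm pairs carry the trial's hypothesis (end of section 1), and two of them, combined versus EMT and combined versus PA, set the sample size. The pilot SDs differ by a factor of 18.717 / 2.828 = 6.6 between combined and PA and by 18.717 / 7.638 = 2.45 between combined and EMT. A normality test does not examine this, so data can pass it in every arm and still break the equal-variance assumption.

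**Working it through.** **Inputs.** From section 2.4: pilot change SDs C = 18.717 (combined), E = 7.638 (EMT) and P = 2.828 (PA); alpha 0.05; power 80%; 20 per arm before the dropout allowance. Assumptions: normal data; all six pairs tested, so 0.05 / 6 = 0.0083 per pair; control SD D, which is not given, set to 2.828, 7.638 or 18.717.

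**1. The plan's own figure.** For combined versus EMT, the pair SD is sqrt((18.717² + 7.638²) / 2) = 14.29 and the difference is 39.33 − 26.33 = 13.00. An equal-variance t test at two-sided 0.05 and 80% power needs 20 per arm. For combined versus PA, the pair SD is 13.39, the difference 19.33 and the requirement 9. Both match section 2.4. The sample size therefore rests on pair-specific SDs, whereas the analysis pools over four arms.

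**2. Standard errors at 20 per arm.** Separate-variance SE = sqrt((s1² + s2²) / 20):
- combined vs EMT: 4.52
- combined vs PA: 4.23
- EMT vs PA: 1.82

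Pooled SE = sqrt(2 × MSE / 20), with MSE = (C² + E² + P² + D²) / 4:

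| Control SD | MSE | Pooled SE | Ratio to separate SE: combined vs EMT | combined vs PA | combined vs control | EMT vs PA |
|---|---|---|---|---|---|---|
| 2.828 | 106.2 | 3.26 | 0.72 | 0.77 | 0.77 | 1.79 |
| 7.638 | 118.8 | 3.45 | 0.76 | 0.81 | 0.76 | 1.89 |
| 18.717 | 191.7 | 4.38 | 0.97 | 1.03 | 0.74 | 2.40 |

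The pooled SE is too small for a pair when MSE is below the mean of that pair's two variances. For combined versus EMT this means D below sqrt(C² + E² − P²) = 20.0. For combined versus PA it means D below sqrt(C² + P² − E²) = 17.3.

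**3. False-positive rates if change scores are analysed** (simulation, equal means, pooled test with Bonferroni, nominal 0.83% per pair):

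| Control SD | combined vs EMT | combined vs PA | combined vs control | Family-wise |
|---|---|---|---|---|
| 2.828 | about 6% | about 4.7% | about 4.6% | about 8% |
| 7.638 | about 4.6% | about 3.4% | about 4.6% | about 7.4% |
| 18.717 | about 1.2% | about 0.7% | about 5.2% | about 6.6% |

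Bonferroni-adjusted Welch tests stay at about 0.8-0.9% per pair and 3.3-3.7% family-wise in all three cases. For EMT versus PA the error runs the other way. The pilot difference of 26.33 − 20 = 6.33 points is detected about 13%, 8% or under 1% of the time with the pooled test, against 72% with Welch.

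**4. If scores at T1 and T2 are analysed.** Visit scores also carry baseline spread. Assume a common baseline SD of 10, 20 or 30, independent of change, and a control change SD of 7.638. The combined-to-PA SD ratio falls from 6.6 to 2.04, 1.36 or 1.17. The combined versus EMT error is then about 2.5%, 1.4% or 1.1%, and family-wise error about 5.3%, 4.3% or 4.1%.

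**The case against.** Four points can fairly be made for the plan.

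- **The SDs may belong to another variable.** They describe change, while section 2.12 compares groups at T1 and T2. This stands. Step 4 shows that with visit scores the family-wise inflation essentially disappears and only a mild distortion of single pairs remains.
- **The pilot evidence is thin.** Its size is not stated. The means and SDs would fit whole-number changes in 3, 3 and 2 patients, though that is an inference. If so, the 95% interval for the combined-to-PA SD ratio runs from about 0.23 to 41, and a test of equal variances gives p of about 0.21. This stands as a limit on the size of the problem. It is not evidence that variances are equal, and the sample size relies on the same SDs.
- **The control SD is unknown.** A reader might infer that the key comparisons will have standard errors that are too small. The document does not support that as a fact. At a control SD of 18.7 the ratio is 0.97 for combined versus EMT and 1.03 for combined versus PA, so the bias nearly vanishes or reverses.
- **A variance check is detail that an article may leave to the analysis plan.** Its mere absence would be no finding. However, section 2.12 states a complete rule for choosing the test, and normality alone decides it.

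A reader might also infer that PA versus control and EMT versus control become almost undetectable. No control mean or SD is given. With the pilot gains of 20 and 26.33 and an assumed control gain of 0, the pooled test has 97-100% power for both pairs over control SDs of 2.8 to 18.7. PA versus control becomes hard to detect only if control patients improve nearly as much as PA patients.

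**Conclusion.** The concern holds in a conditional form. Section 2.12 fixes an equal-variance method on a check that does not examine variances, and the plan's own pilot figures cast doubt on the assumption. If change scores with those SDs are analysed at 20 per arm, the combined versus EMT false-positive rate is about 1.2-6% against 0.83%, depending on the control SD, and family-wise error is about 6-8%. EMT versus PA loses most of its power. If visit scores are analysed, the pair error is about 1.1-2.5% and family-wise error about 4-5%, for an assumed baseline SD of 10-30 and a control change SD of 7.6. All of this treats imprecise pilot SDs as true and assumes normal data and six tested pairs. The case for change is that the safer method costs little. It is not shown that the planned analysis will give a wrong answer.

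**What to change.** In section 2.12, before any unblinded analysis:

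- State whether the score at T1 and T2 or the change from baseline is analysed.
- Replace the normality-based choice with Welch ANOVA and pairwise comparisons that do not pool variances (Games-Howell, or Welch t tests with Bonferroni adjustment), used whatever the Kolmogorov-Smirnov result.
- Keep Kruskal-Wallis as a sensitivity analysis.

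The change is to wording only, and no extra data are needed. If variances are in fact equal, about 2-3 points of pairwise power are lost at 20 per arm. If the pilot change SDs hold, intervals for combined-arm pairs become wider. With a control SD of 7.638, the unadjusted 95% half-width for combined versus EMT goes from 6.9 to 9.3 BIT-C points, which is the uncertainty those SDs imply.

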**Figure 1 F1:**
[figure not shown]
Flowchart of the study design. PA, prism adaptation. EMT, eye movement training.

**Table 1 T1:** Schedule of enrollments, interventions, and assessments.

		**Screening**	**Randomization**	**Intervention**	**Follow up**
**Time point**		**Within one weeks**	**Day 0**	**2 weeks** **(10 sessions)**	**Post-2 weeks**
			**T** _0_	**T** _1_	**T** _2_
Enrollments	Informed consent	√			
	Demographic characteristics	√			
	Medical history	√			
	Eligibility assessment	√			
	Radom allocation		√		
Intervention	Conventional rehabilitation			√	
	PA			√	
	EMT			√	
	PA & EMT			√	
Assessment	Cognitive level (MMSE)	√		√	
	Behavioral inattention test-conventional subset			√	√
	Catherine bergego scale			√	√
	Modified barthel index			√	√

PA, prism adaptation; EMT, eye movement training; MMSE, Mini-mental State Examination.

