### 2.7. Baseline data

Baseline data are collected after informed consent and before randomization. The baseline assessment includes demographic characteristics such as sex, age, time of onset, cause of damage, and assessment scales including the Mini-Mental State Examination, Catherine Bergego Scale, Behavioral Inattention Test-Conventional Subset (BIT-C), and Modified Barthel Index (MBI). All baseline data will be collected *via* paper forms.

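### The one-way ANOVAs at T1 and T2 have no baseline term although the baseline scores are collected: the test is valid but gives away precision, and the text does not say whether raw or change scores are analysed

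*Protocol article*

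**What the plan says.** **Analysis (protocol article, 2.12).** "one-way ANOVA will be used to examine the effectiveness of intervention between the 4 groups at T1, T2". Pairwise comparisons follow with a Bonferroni correction, and Kruskal-Wallis is used if normality is not confirmed. The section names no covariate, change score or repeated-measures model. The significance rule is "2-tailed *P* < 0.05 will be considered a statistically significant difference".

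**Baseline comparisons (2.12).** "Age, time of onset, and MMSE will be analyzed by ANOVA or Kruskal-Wallis test"; sex and cause of damage are compared by chi-square. BIT-C, CBS and MBI are not in the list.

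**Baseline data (2.7).** "Baseline data are collected after informed consent and before randomization". The scales named there are the MMSE, CBS, BIT-C and MBI.

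**Sample size (2.4).** The quantity used is "the changes in BIT-C scores before and after the intervention", with 39.33 (SD 18.717) for the combined group, 26.33 (SD 7.638) for EMT and 20 (SD 2.828) for PA. The result is 20 per group for combined against EMT, 9 per group for combined against PA, and 22 per group after allowance for dropout.

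**Randomization (2.5).** 88 random numbers are ranked and cut into four blocks of 22. No stratification by severity of neglect is described.

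**Schedule (Table 1).** The rows for "Behavioral inattention test-conventional subset", the Catherine Bergego Scale and the Modified Barthel Index are ticked only in the intervention (T1) and follow-up (T2) columns. The MMSE row has a screening tick.

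**The concern.** A one-way ANOVA has group as its only factor. If it is run on the score at T1 or T2, all between-patient variation in initial neglect stays in the error term, and any chance difference in starting severity between arms stays in the estimated effect. Entry is wide: patients are 1 to 12 weeks after onset (2.2.1), are excluded only below 8 on star cancellation (2.2.2), and must have cancelled fewer than 52 stars (2.3). With about 20 completers per arm and no stratification, baseline adjustment is the obvious protection, and the values it needs are already collected.

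The 80% power in 2.4 belongs to change scores, whereas 2.12 describes a comparison at T1 and T2. Depending on what is analysed, the trial may have less or more power than planned, and the article does not let the reader tell which.

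**Working it through.** **1. Reproduce the plan's figure.** Inputs from 2.4: "the probability α of occurrence of the Type I error was set to 0.05"; power of 0.80 (a type II error of 0.2); means and SDs of change as above. Two-sided testing is from 2.12.

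- Difference, combined minus EMT: 39.33 − 26.33 = 13.00.
- Common SD of change: √((18.717² + 7.638²)/2) = 14.29.
- Noncentrality with 20 per arm: 13 / (14.29 × √(2/20)) = 2.876. The two-sided t-test on 38 df has power 0.800.
- The same method for combined against PA (difference 19.33, SD 13.39) gives 9 per arm with power 0.820.

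The stated 20 and 9 are reproduced, so the planned 80% is the power of a t-test on change scores.

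**2. Translate to the three possible analyses.** The correlation ρ between baseline and follow-up BIT-C is not in the document and is assumed over a range. Baseline and follow-up variances are assumed equal. The change SD is held at the protocol's 14.29.

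- Raw follow-up score: var(change) = 2σ²(1 − ρ), so σ = 14.29 / √(2(1 − ρ)).
- Change score: SD = 14.29 at every ρ.
- ANCOVA on baseline: SD = σ√(1 − ρ²), which equals 14.29 × √((1 + ρ)/2).

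The last expression is below 14.29 for any ρ below 1, and σ√(1 − ρ²) is below σ for any non-zero ρ. ANCOVA therefore has the smallest residual SD of the three throughout the range.

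**3. Power for a 13-point difference, 20 per arm, two-sided 0.05 (t-test, 38 df).**

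| ρ (assumed) | SD raw | SD ANCOVA | Power raw | Power change | Power ANCOVA |
|---|---|---|---|---|---|
| 0.3 | 12.08 | 11.52 | 0.91 | 0.80 | 0.94 |
| 0.5 | 14.29 | 12.38 | 0.80 | 0.80 | 0.90 |
| 0.6 | 15.98 | 12.79 | 0.71 | 0.80 | 0.88 |
| 0.7 | 18.45 | 13.18 | 0.58 | 0.80 | 0.86 |
| 0.8 | 22.60 | 13.56 | 0.43 | 0.80 | 0.84 |

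The one degree of freedom spent on the covariate lowers the ANCOVA figures by less than 0.001. The 0.05 level is the one used in 2.4, without the Bonferroni correction.

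Raw and change scores break even at ρ = 0.5, where 2(1 − ρ) = 1. Below that the raw score has more power than planned; above it, less.

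**4. Chance imbalance, for ρ = 0.7.** The standard error of the baseline difference between two arms of 20 is 18.45 × √(2/20) = 5.84 points. For a baseline difference of that size:

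- a raw-score comparison carries 0.7 × 5.84 ≈ 4.1 points into the estimate;
- a change-score comparison carries (1 − 0.7) × 5.84 ≈ 1.8 points, in the opposite direction (regression to the mean);
- ANCOVA removes the linear part.

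The target difference is 13 points.

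**5. Table 1 against the text.** Section 2.1 gives three assessment visits including baseline, and 2.7 lists BIT-C, CBS and MBI among the baseline measures. Table 1 has no baseline tick for any of the three. The MMSE screening tick in the same table makes a fault in extracting the table an unlikely explanation.

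**The case against.** **The authors may mean change scores.** Sections 2.8.2 and 2.8.3 describe the scales as measuring changes, and 2.4 uses change. On that reading the 80% basis is kept. This stands: a reader might infer that the planned power does not apply, but the article does not support that as a flat statement. What remains is that the analysed variable is not stated, and that ANCOVA would still be more efficient (0.86 against 0.80 at ρ = 0.7).

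**Even on raw scores, a shortfall is conditional.** It appears only above ρ = 0.5, and no ρ is given. This also stands. A reader might instead assume a raw-score SD of 20, 25 or 30 and obtain unadjusted power of 52%, 36% or 27%. Those SDs are not in the article. Under equal variances they agree with its change SD only if ρ is about 0.74, 0.84 or 0.89, so they show only the unfavourable side.

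**The unadjusted test is not invalid.** Under randomization it is unbiased, keeps its type I error, and has a standard error that already allows for chance imbalance. A reader might infer that imbalance will dominate or bias the result; the documents do not support that. The issue is precision, together with the error in this one trial's estimate that a known baseline difference would explain.

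**The analysis plan may settle it.** A separate plan could specify adjustment. But the article does not leave the method open: it names a one-factor test and a one-factor fallback.

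**Table 1 may be only editorial.** BIT-C is needed for eligibility (2.2.1) and eligibility assessment is ticked at screening, so a missed baseline BIT-C is unlikely. This is fair for BIT-C. It does not cover CBS and MBI, which are not eligibility measures.

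**Conclusion.** The point holds as a matter of efficiency and clarity, not validity. Section 2.12 fixes an unadjusted comparison at T1 and T2, leaves open whether raw or change scores are compared, and makes no use in the efficacy test of the baseline scores that 2.7 collects.

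Over ρ from 0.3 to 0.8, ANCOVA gains 0.04 to 0.14 in power over change scores and 0.03 to 0.41 over raw scores. Whether the planned 80% is lost depends on the reading: not with change scores, and with raw scores only above ρ = 0.5.

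These figures rest on the pre-experiment's change SD of 14.29, equal variances at baseline and follow-up, an assumed ρ, 20 completers per arm and the 13-point BIT-C contrast. The article gives no figures for the same calculation on CBS or MBI. The recommendation does not depend on the value of ρ, since ANCOVA had the highest power at every value checked. The change should be made. The Table 1 discrepancy is real but secondary.

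**What to change.** In 2.12, for each of BIT-C, CBS and MBI, replace the one-way ANOVAs by ANCOVA at T1 and T2, with group as factor and the baseline value of the same scale as covariate. One repeated-measures model over T1 and T2, with group, time, group-by-time and the baseline value, would serve equally well. State that the follow-up score is the dependent variable. Keep the Bonferroni-corrected pairwise contrasts, now on adjusted means. Replace the Kruskal-Wallis fallback by a baseline-adjusted rank-based or robust analysis, used if the model residuals are clearly non-normal.

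Reconcile Table 1 with 2.1 and 2.7 by showing the baseline assessment of BIT-C, CBS and MBI, because the adjusted analysis needs those values.

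Cost: a rewording of 2.12 and a correction to Table 1. If baseline scores are taken as 2.7 describes, no extra patients or measurements are needed. The article says recruitment was ongoing, so the wording could be settled before analysis.

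### Within each four-arm comparison, single-step Bonferroni is needlessly conservative; Holm-adjusted Welch p-values would recover some power for combined therapy versus eye movement training (EMT) at almost no cost

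*Protocol article*

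**What the plan says.** Section 2.12 gives the between-group analysis for normally distributed data: "one-way ANOVA will be used to examine the effectiveness of intervention between the 4 groups at T1, T2, with Bonferroni correction for multiple comparisons". These comparisons are labelled post hoc. The significance criterion is "2-tailed *P* < 0.05 will be considered a statistically significant difference". The section does not give the number of pairs in the correction, and it does not say that pairs are tested only after a significant F. Four arms with no subset named is most naturally read as all six pairs, so 0.05/6 = 0.0083 per pair.

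Section 2.4 shows which pair is hardest to win. The pilot BIT-C change with both treatments was "39.33 ± 18.717 for the combined intervention group". Each single treatment did less well: "26.33 ± 7.638 for the eye-movement training group", compared with only "20 ± 2.828 for the PA training group". From these, "the combined intervention and eye-movement training groups required 20 samples each", against 9 each for combined versus prism adaptation (PA). On false positives the section says that "the probability α of occurrence of the Type I error was set to 0.05". On power it says that "the probability β of occurrence of the Type II error was calculated as 0.2". No pilot figures are given for the control arm.

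**The concern.** Single-step Bonferroni holds every pair to 0.05/6, however many of the other pairs have already been separated. With four arms, once any true difference exists, at most three of the six pairwise null hypotheses can still be true, so a fixed divisor of six leaves part of the 5% unused.

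Holm compares the ordered p-values with 0.05/6, 0.05/5, 0.05/4, 0.05/3, 0.05/2 and 0.05, stopping at the first failure. On the same valid p-values it rejects everything that Bonferroni rejects and sometimes more, with the same familywise guarantee.

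The price of the stricter rule falls on combined versus EMT. This contrast set the sample size, and it bears directly on the hypothesis that the combination is better.

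**Working it through.** **Inputs.** From section 2.4: pilot means 39.33, 26.33 and 20; SDs 18.717, 7.638 and 2.828; 20 evaluable per arm. From section 2.12: two-tailed 0.05 and Bonferroni. Assumed, because the article gives no values: control gain 5 to 26 points; control SD 2.828, 7.638 or 18.717; six pairs; BIT-C change as the scale analysed.

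**1. Reproducing the plan's figure.** Difference 39.33 − 26.33 = 13.00. Pooled SD = √[(18.717² + 7.638²)/2] = 14.29. SE = 14.29 × √(2/20) = 4.52. Noncentrality = 13.00/4.52 = 2.88. At two-sided 0.05 with 38 df the critical value is 2.02 and power is 80.0%. The stated 20 per group is reproduced.

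**2. The same contrast at 0.05/6.** With a common SD of 14.29 and the pooled error of four arms (76 df), the critical value is 2.71 and power is 57%.

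**3. Familywise error at one scale and one time point** (simulation, 20 per arm; Bonferroni with a common SD is shown with the F gate, which the article does not state):

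| True pattern | Bonferroni, common SD | Bonferroni, pilot SDs, Welch |
|---|---|---|
| All four arms equal | 3.8% (4.1% ungated) | 3.3–3.6% |
| Three equal, one different | about 2.2% | about 2.0–2.3% |
| Two equal pairs | 1.7% | about 1.6–1.7% |

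Holm stays at about 5% or below in all of these settings.

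**4. Power for combined versus EMT, 20 per arm, control gain 5 to 26 points:**

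| Setting | Bonferroni | Holm | Gain in points |
|---|---|---|---|
| Common SD 14.29, pooled error | 57% | 62–73% | 62 − 57 = 5 to 73 − 57 = 16 |
| Pilot SDs, Welch | 51–52% | 59–78% | about 7 to 26 |

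The gain is smallest when the control gain is close to the EMT gain. It is largest when control lies well below the active arms, because the other pairs are then rejected first and the divisor falls. At 22 per arm with a common SD of 14.29, Bonferroni has about 62% and Holm 68–78%.

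**5. Why Welch has to go with it.** The usual ANOVA post hoc test uses one pooled error for every pair. With the pilot SDs that error is too small for pairs involving the combined arm. Gated Bonferroni then runs at about 6.1–7.6% when all arms are equal. With two equal pairs, configurations in which Bonferroni gives about 4.6–6.1% go to about 9–11% under Holm. Welch p-values remove this inflation.

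**The case against.** The strongest reply is that nothing in 2.12 is wrong. Bonferroni is a valid procedure, the article nowhere says that the familywise error equals 5%, and the choice of step-down method could be refined in an analysis plan that is not shown. This stands, and it limits the point to an efficiency suggestion.

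A reader might infer four stronger things that the documents do not support.

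- *That the plan over-corrects the trial as a whole.* Section 2.8.2 names two primary scales and 2.12 tests at two time points, with no stated correction across these four analyses. With equal SDs and no true differences, the planned procedure applied four times has an overall error of about 8% (correlation 0.9) to 15% (independent).
- *That the ANOVA gate does the damage.* The gate is not stated. If it is applied with equal SDs, it lowers the all-equal error only from 4.1% to 3.8%. In both the equal-SD and the pilot-SD simulations it changes power for combined versus EMT by less than 0.1 point. The loss comes from the fixed divisor.
- *That the familywise error is 2–4% whatever the variances.* Step 5 shows it above 5% with pooled error and the pilot SDs.
- *That the gain is free.* Holm on pooled-error p-values could increase false positives here.

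The power figures also depend on an assumed control arm. At a control gain of 26 points the gain in power is about 5 points with a common SD. With pilot SDs and pooled error, Bonferroni power would be 60–82%, but that comes from the understated error in step 5 and is not a sound baseline.

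**Conclusion.** The point holds as a cheap, optional improvement. Within one scale at one time point, single-step Bonferroni over six pairs uses about 1.6 to 4% of the available 5% when the p-values are valid. Holm recovers roughly 5 to 16 points of power on combined versus EMT with a common SD, or 7 to 26 points with the pilot SDs and Welch tests.

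This rests on reading six pairs into 2.12, on the pilot means and SDs, on the assumed control arm, and on analysing BIT-C change. It concerns only the normal-data branch of the analysis.

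It should not be read as a rescue of the sample size. Section 2.4 planned 80% at an unadjusted 0.05. Even after the change, power in these settings is 59–78% at 20 per arm. Multiplicity across scales and time points is a separate matter that this leaves untouched.

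**What to change.** In section 2.12, replace the Bonferroni phrase with a statement that the six pairwise p-values in each four-group comparison will come from unequal-variance (Welch) t-tests and be adjusted by Holm's step-down method at a two-sided familywise 0.05. State that all six pairs form the family. Holm needs no significant F for its error control, so the text should also say whether the ANOVA result is a condition for pairwise testing. Set this before any outcome is compared by arm.

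The cost is one sentence and a short calculation on six p-values outside the ANOVA post hoc output, with no extra patients or data. The drawback is that step-down tests have no equally simple simultaneous confidence intervals. Bonferroni-adjusted or unadjusted intervals could be reported alongside, labelled as such.
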